### Sample size

There are currently 6518 students enrolled in the 10^th^ and 11^th^ grades in State-financed schools in the commune of Santiago. Using a 99% confidence level and a 5% error margin, the sample framework is 605 students, which will be divided into the study and control groups. The statistical power is determined using an analysis of variance with a significance level of 0.05, a sample size of 605 and an expected difference of 0.2 points between groups, which will provide a statistical power of at least 0.8. The 0.2 difference is the smallest reported in previous studies comparing the scores of two groups with the instruments that will be used; it was reported in the analysis of the scores of the scale of ambivalent sexism [24].

The statistical power was calculated using the software G*Power [25]. After making a slight adjustment due to the number of students currently enrolled in each school at each level, the definitive size of the experimental phase of the study will be 609 students.

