The result variables of the intervention will be the following: (a) change in knowledge of sexuality manage correctly information on topics related to the biological components of sexuality such as reproduction, prevention of STI and pregnancy, among others; (b) change in preventive sexual behavior, which may be related to (i) behavior or intention to prevent STI and pregnancy, or (ii) sexual abstinence or intention to postpone initiation of sexual life; (c) change in gender attitude related to (i) positive disposition towards persons of different genders and sexual orientation, and (ii) empowering in sexuality of LGBT and female students; (d) change in components of mental health related to sexual health, decrease of internalizing-externalizing symptomology, and improvement in self-efficacy (Table 2). The following instruments will be used:*Knowledge test* [33]. This is a 34-item multiple choice instrument which was designed to evaluate the effectiveness of interventions in sexual education to improve knowledge on sexuality in adolescents; it evaluates areas including pregnancy, STI, physical development, and others. Its reliability is *α* = 0.89.*Ad hoc survey*. It was elaborated by the research team to evaluate the behavior and intention of preventive behavior in sexuality, self-efficacy. and empowerment in sexuality in LGTB and female students. Ad-hoc surveys have been used and reported in other randomized controlled trial of interventions in sexual health (e.g.. Coyle [34], Goesling [35]. and Yakubu [36]). This survey will follow the guidelines developed by Manaseri [37] and Jirapongsuwan [38].*Scale for detection of sexism in adolescents (DSA)* [39]. This is an instrument of 26 items developed for adolescents. It evaluates sexism (attitude of superiority towards women), differentiating between hostile and benevolent sexism. The response scale for the items is a Likert type with six alternatives (from 1 = disagree completely to 6 = agree completely). Its reliability is *α* = 0.881.*Scale of negative attitudes toward trans persons (NATP)* [40]. It measures attitude as an expression of prejudice towards trans persons. It has nine items with a Likert scale with five response options, from 1 = disagree completely to 5 = agree completely. Its reliability is *α* = 0.886.*Short version of modern homophobia scale* [41]. It measures homophobic attitudes in the dimensions of personal discomfort, institutional, and deviation/changeability. It is composed of 46 items that evaluate attitudes towards lesbians and gays on a Likert scale of 1–5. Its reliability is *α* = 0.80.*Pediatric symptom checklist (PSC-17)* [42]. This is an abbreviated version of the 35-item PSC [43]. It evaluates general psychosocial functioning, detecting emotional and behavioral difficulties in children and adolescents [44]. Its reliability is *α* = 0.72. PSC-17 is self-administered by adolescents, evaluating the existence of internalizing difficulties (e.g., despair and sadness), externalizing difficulties (e.g., difficulties in social relations such as disobedience of norms and fights with others), and attention difficulties (e.g., difficulty in concentration -60,66-). As in other studies (e.g., Penner [45]), this instrument will be used to evaluate the adolescents’ mental health. The baseline and follow-up evaluations will be obtained confidentially, and be recorded in files managed by the team responsible for the study.

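### The 80% power claim rests on 0.2 raw points from a scale that matches no listed instrument by name, and without an SD it cannot be shown to hold for any outcome

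*Protocol article*

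**What the plan says.** The Sample size section of the protocol article does two separate things. It first obtains 605 students from a survey-precision formula (6518 enrolled, 99% confidence, 5% margin). It then adds a power statement: "The statistical power is determined using an analysis of variance with a significance level of 0.05, a sample size of 605", with "an expected difference of 0.2 points between groups", "which will provide a statistical power of at least 0.8". The calculation is credited to G*Power, and the total is then adjusted to 609.

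On the origin of the 0.2, the section says "The 0.2 difference is the smallest reported in previous studies comparing the scores of two groups with the instruments that will be used" and continues "it was reported in the analysis of the scores of the scale of ambivalent sexism", citing reference 24.

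The Outcomes section and Table 2 list a 34-item multiple-choice knowledge test, an ad hoc survey, the DSA (26 items, scored 1 to 6), a scale of negative attitudes to trans persons (9 items, 1 to 5), a homophobia scale (46 items, 1 to 5) and the PSC-17. The Objectives section sets four hypotheses: knowledge, preventive behaviour, gender attitude and mental health. The power statement is tied to none of them.

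**The concern.** There are two linked problems.

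**Source.** The 0.2 is presented as coming from the trial's own instruments, but the scale named does not appear under that name in Outcomes or Table 2. A reader cannot tell which outcome the planning value describes.

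**Unit.** The plan takes the smallest difference in raw points across several instruments as its planning value. That is cautious only if a point means the same on each of them. Detectability depends on the difference divided by the SD, and the instruments differ in number of items and in response range. The section gives no SD, no scoring convention (item mean or sum) and no standardised effect.

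At stake is how the results are read. A single unqualified power figure placed beside four hypotheses invites the reader to treat a null result on, say, knowledge or the PSC-17 as coming from an adequately powered comparison. Nothing in the document shows that it would be.

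**Working it through.** **Inputs from the document.** Significance level 0.05, ANOVA on two groups (equivalent to a two-sided test), difference 0.2 points, N = 605 in the power statement, and 301 study and 308 control students in Table 1. The SD is not given.

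**1. The plan's 605.** The finite-population formula for a proportion of 0.5 is n0 = z² × 0.25 / 0.05² and n = n0 / (1 + (n0 − 1)/6518). With z = 2.58, n0 = 665.64 and n = 604.05, rounded up to 605. This reproduces the stated figure. The 0.2 does not enter it.

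**2. The plan's power.** It cannot be reproduced from the stated inputs, because the SD is missing and the unit is undefined. The readings tried at N = 605 are:

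| Reading of 0.2 | Power |
|---|---|
| Standardised difference (Cohen's d), two-sided | 0.69 |
| The same, one-sided | 0.79 |
| Cohen's f | 0.998 |
| d = 0.2 (f = 0.1), between-group test averaged over three occasions, assumed correlation 0 to 0.7 | 0.99 down to 0.78 |

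Whether the claim passes depends on a choice that the section does not state.

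**3. What 80% power requires.** Treat students as independent, 301 against 308, two-sided 0.05.

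- Standard error in SD units: √(1/301 + 1/308) = 0.0810.
- Detectable standardised difference: (1.960 + 0.842) × 0.0810 = 0.227.
- Largest SD at which 0.2 points reaches 80%: 0.2 / 0.227 = 0.88 points.

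**4. Power for 0.2 points under assumed SDs**, from Φ(0.2 / (SD × 0.0810) − 1.96):

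| Assumed SD (points) | Power |
|---|---|
| 0.6 | 0.98 |
| 0.8 | 0.87 |
| 0.88 | 0.80 |
| 1.0 | 0.69 |
| 1.2 | 0.54 |

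These SDs are illustrations, since the document supplies none.

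**5. What 0.2 points means on each instrument**, as a share of the possible range:

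| Instrument | Item mean | Sum score |
|---|---|---|
| DSA (26 items, 1–6) | 0.2/5 = 4% | 0.2/130 = 0.15% |
| Trans-attitudes scale (9 items, 1–5) | 0.2/4 = 5% | 0.2/36 = 0.56% |
| Homophobia scale (46 items, 1–5) | 0.2/4 = 5% | 0.2/184 = 0.11% |
| Knowledge test (34 items, assuming one point each) | not applied | 0.2/34 = 0.59% |

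The same raw figure is a very different effect from one score to another, so a minimum taken over raw points does not identify the hardest outcome to detect.

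**6. Clustering.** Table 1 puts each of the ten schools wholly in one arm, on average 609/10 = 60.9 students per school. The 0.227 would be multiplied by about √(1 + 59.9 × ICC), which exceeds 1 for any positive intraclass correlation. It is therefore a best case.

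**The case against.** The strongest objection concerns the source. A reader might infer that the ambivalent sexism scale is not administered at all, so that the 0.8 applies to no planned endpoint. The document does not support that. It describes the DSA as separating hostile from benevolent sexism, so the phrase in Sample size may be a loose name for the DSA, which would agree with the claim that the value came from the trial's own instruments. Reference numbers do not settle it either. The DSA is reference 39 in Outcomes and 48 in Table 2, and the knowledge test is 33 in one place and 46 and 47 in the other. Reference 24 may be a study that used the scale rather than its source. This part of the objection stands.

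A reader might also apply 0.2 points to a knowledge or PSC-17 total and conclude that power there is negligible. That does not follow. The plan does not predict 0.2 points on those scores, and neither their SDs nor their scoring is given.

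It is also fair to say that the 0.8 is not shown to be false. It holds, with students independent, for any score with an SD of 0.88 points or less, and some other readings of the 0.2 reach it. The section also makes no explicit claim of power for each hypothesis, and a journal article may leave SDs for every instrument to a fuller document.

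What the objection does not remove is the rule that the section itself states. It uses a minimum over raw points from scales with different metrics to support a single unqualified power figure. Even if the DSA is meant, the value informs one outcome, and still without an SD.

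**Conclusion.** The point holds as a flaw in what the section states. The scale named as the source matches no listed instrument by name and needs reconciling. The smallest raw difference is not a conservative planning value across these instruments. The claim of at least 0.8 is not supported by its stated inputs: 80% power needs about 0.227 SD (an SD of at most 0.88 points), and 0.2 SD gives about 0.69.

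These figures assume a two-sided 5% comparison of 301 and 308 independent students at one time point, with a normal approximation. Allocation by school makes them optimistic. The point does not extend to saying that the scale is absent from the battery, that no outcome could be covered, or that power for the knowledge test or PSC-17 has any particular value. The effect on the trial is limited because the 605 came from the survey formula. What needs correcting is the power statement, not the enrolment.

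**What to change.** Rewrite the power paragraph in Sample size:

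- Reconcile the source sentence with Outcomes and Table 2. Either say that the DSA is meant and give the study that reported the 0.2, or correct the statement that the value came from the trial's instruments.
- Name the one instrument and score (item mean or sum) to which the power figure applies, and give the effect in SD units with the SD used.
- Replace the unqualified 0.8 with the power, or the detectable standardised difference, at the fixed 609. Before clustering this is about 0.227 SD at best. The reported figure should allow for allocation by school, with the assumed intraclass correlation stated, and will be larger.
- State that the figure does not cover the knowledge, behaviour or PSC-17 outcomes unless it is shown for each.

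The cost is a revised paragraph and, if several outcomes are covered, a short table. Enrolment is unchanged. The downside is a less favourable stated power.

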### Randomization

The assignment of the participants to the groups will be implemented in a two-stage selection of the students; since there are already existing teaching-learning processes in process in the schools, with their time limitations, we will have to choose entire “courses” (in Chilean secondary schools, a course is a group of about 40 students who have all classes together) rather than choose individual students.

We will establish groups among the schools to compensate for their different sizes; some schools in the commune are much larger than others (four or more courses per grade. Thus, we will divide the schools into two blocks: one with the largest schools and one with the medium- and small-sized schools. In the second stage, courses that meet the inclusion criteria to participate in the study will be selected randomly within each block. Table 1 details the distribution of the samples.

**Table 1 Tab1:** Samples to be selected

	**Study group** **No. of students per grade**		**Control group** **No. of students per grade**		
**School**	*10th grade*	*11th grade*	*10th grade*	*11th grade*	Total
*1*	---	---	31	28	59
*2*	---	---	33	27	60
*3*	---	---	34	34	68
*4*	---	---	26	30	56
*5*	---	---	33	32	65
*6*	29	27	---	---	56
*7*	29	30	---	---	59
*8*	28	29	---	---	57
*9*	25	31	---	---	56
*10*	*40*	*33*	---	---	73
	151	150	157	151	
**Sample totals**	**301**		**308**		**609**

### Allocation process

The allocation sequence will be generated using random numbers produced by the statistical program R. A single investigator will carry out both the sequence of participants’ assignments and their assignment to each group ([name]).

To ensure a blind analysis, the professional in charge of data analysis ([name]) will not know to which group the participants belong. Therefore, the database will be anonymized by assigning codes, which will only be known by another team professional ([name]). Unmasking is not considered to be permitted under any circumstances.

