### Participants: eligibility criteria

The intervention will be directed exclusively to students of the 10^th^ and 11^th^ grades who are enrolled in one of the education establishments that depend on the Municipality of Santiago. The inclusion criteria for these schools will be the following: (i) have students of these grades enrolled; (ii) not being an education center oriented to adults or persons deprived of liberty (e.g., closed or semi-closed compounds of Gendarmería de Chile or the National Service for Minors); (iii) have regularity in teaching and learning (for example, schools that were not partially interrupted in 2022 by student manifestations); and (iv) have informed consent of the director. The inclusion criteria for the students will be (i) having 90% or greater attendance in classes: (ii) providing informed consent of voluntary participation; and (iii) having explicit and informed consent of their parents or guardians.

The selected students will be randomly divided into the study and control groups; the intervention will take place in the same schools that the students attend. The assignment to groups will use simple random sampling, performed in two stages. In the first stage, the available schools will be randomly assigned to the study and control groups, while the second stage will randomly select the groups in each school that will participate. The study groups will receive a 10-session intervention in sexual education, covering topics related to preventive sexual conduct, gender equity, and mental health. The control groups will not receive intervention; they will continue with the sexual orientation that each school provides to its students. Sexual orientation is general and is provided by the Ministry of Education. The goal is to evaluate and diagnose the behaviors and reproductive health needs of adolescents, addressing the values adopted regarding the decision to engage in sexual relationships and/or have multiple sexual partners, as well as perceptions of risk.

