### Intervention: description of Focus-on

Focus-on is a comprehensive program of sexual education for adolescents. Its design follows the guidelines of the Intervention Mapping Approach [26] and the orientations proposed by the Framework for Gender-Transformative Health Promotion [16]. Specifically considered are (i) the theories, contents, and strategies of the randomized controlled trial of comprehensive interventions for adolescents performed in the last 10 years [27]; and (ii) the results of a previous study in the object population on the implementation of an intervention in sexual health education. Both studies were done by the team that created the program.

The program is based on three fundamental theories as transverse axes: the Theory of Planned Behavior [28], the Framework for Gender-Transformative Health Promotion [16], and the Ecological Focus of Human Development [29]. Some sessions will use the precepts of the Theory of Social Learning [30], the Cognitive-Behavioral Theory using the emotion-regulating model of Gross [31], and the Transtheoretical Change Model [32].

The intervention has a participative focus, thus the activities are designed to promote processes of knowledge, understanding, application, analysis, and reflection in the adolescents. The activities aim to improve the capacity for critical thinking, favor the retention and communication of the new information, increase the motivation to listen and learn actively, and to improve interpersonal abilities. The execution of the intervention uses three pillars: (i) preventive sexual behavior; (ii) gender equity; and (iii) mental health. These pillars approach their different objectives -promote preventive sexual behavior, gender equity in sexual health, and improve aspects of mental health related to sexuality.

The intervention consists of ten weekly sessions, each lasting 1 h, which (except the first, which is an introduction to the program) treat these pillars gradually, from the basic to the most advanced aspects. The teams that will perform the intervention will be composed of at least two professionals of the psychosocial area (mainly psychologists, social workers, and/or guidance counselors) of the schools included in the study, who will be capacitated in the correct implementation of Focus-on.

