**Assessments**					
Socio-demographic	Personal and home information (ad hoc survey)		x		
	Social network information		X		
Knowledge about sexuality; preventive behavior in sexuality and behavioral intention; empowering and self-efficacy	Knowledge test [46, 47] Survey ad hoc		x	x	x
Gender attitude	Scale of detection of sexism in adolescents (DSA) [48]	x	x	x	x
	Scale of negative attitudes towards trans persons [40]	x	x	x	x
	Short version of Modern Homophobia Scale [41]	x	x	x	x
Mental health	PSC-17 [42]	x	x	x	x

The enrollment, intervention, and assessments are shown in Table 2.

In each intervention session, we will record the attendance and duration, and using structured observation [49], we will record some elements referring to the implementation of the intervention. Those responsible for executing the intervention will receive bi-monthly supervision to control the evaluation and retention.

No specific retention strategy is planned. Available information for students who drop out will include their socio-demographic data, the number of sessions attended, and the results obtained in the tests administered before dropping out.

Because it will be a mixed experimental design GRTs, at the end of the intervention, we will perform a qualitative Case Study to ascertain the experience of the participants and executors with respect to the program and its implementation. Each school of the study group will be a case. The participants will be students who participated in the program and the executors who implemented the intervention. Each case will include focus groups with the students (at least one per case) and semi-structured interviews with the executors (at least two per case). We will then perform a Qualitative Content Analysis to identify certain emergent topics.

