### Analytical methods

The information that results from the application of the scales will be summarized with descriptive statistics (frequency table, mean, standard error, and asymmetry coefficient) for the pre- and post-intervention evaluations.

Since the intervention has specific objectives for each session, it is not appropriate to impute missing data. However, to account for the potential lack of adherence by some students, it is suggested that participants who miss more than 30% of the sessions should not be included in the data analysis. Regardless of attendance, students will be able to participate in all workshop activities.

We will compare the three evaluations, incorporating information relative to the type of school and course. If the data are normally distributed, we will perform one-way ANOVAs, incorporating post hoc information of the results when necessary, and perform pair-wise comparisons using the Tukey or Games-Howell test.

After the variables with main effects are established, we will perform a factorial ANOVA, in which one of the factors will be fixed (i.e., type of school) and the other will be the repeated measures of the three evaluations. As well as evaluating if the main effects are sustained over time, this will evaluate possible interactions among the studied factors. In this case, following the guidelines proposed by Cohen^75^ for ANOVAs with two or more factors, the effect size will be reported as the partial Eta^2^ statistic. The interpretation of the effect sizes will consider the suggestions of Cohen [50]. These analyses will use the program Jamovi version 1.2 [51].

No interim data analysis will be conducted, and there will be no stopping guidelines.

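### The blind analysis is not secured as written: it rests on participant codes alone, while the attendance exclusion uses a variable that exists only in the study arm

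*Protocol article*

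**What the plan says.** Under Allocation process, the protocol article states that the professional analysing the data "will not know to which group the participants belong". The means is that "the database will be anonymized by assigning codes, which will only be known by another team professional". It adds that "Unmasking is not considered to be permitted under any circumstances".

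Under Analytical methods, it suggests that "participants who miss more than 30% of the sessions should not be included in the data analysis". The wording is impersonal and does not say who applies the rule. The same section says "We will compare the three evaluations, incorporating information relative to the type of school and course". It makes the use of ANOVA depend on normality, leaves the pairwise test as Tukey or Games-Howell, and takes to the factorial ANOVA the variables that have shown main effects.

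The text after Table 2 gives the source of the attendance data: "In each intervention session, we will record the attendance and duration". Under Intervention, "The intervention consists of ten weekly sessions". Under eligibility criteria, "The control groups will not receive intervention"; those schools continue with their usual provision.

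**The concern.** Replacing identities with codes hides who a student is. It does not hide a variable that is filled in for one arm and empty for the other. Session attendance is such a variable, and the plan uses it to decide who is analysed. If the attendance file reaches the analyst, the arm is known before the analysis starts.

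This matters because the analyst's blinding is the only masking the article describes. Principals, teachers and students are told about the intervention, and students complete the instruments themselves. Several analysis decisions are left until the data are seen. Analyst blinding is what would protect those decisions, and a report that claimed it without having secured it would overstate the protection.

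**Working it through.** **Step 1: which arm has the variable.** Attendance is recorded in intervention sessions (text after Table 2). The control groups have no such sessions (eligibility criteria). So a student with a session-attendance record is in the study arm, and a student without one is in the control arm or has missing data.

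**Step 2: where the exclusions can fall.** Re-adding Table 1:
- Control, schools 1 to 5: 59 + 60 + 68 + 56 + 65 = 308.
- Study, schools 6 to 10: 56 + 59 + 57 + 56 + 73 = 301.
- Total: 308 + 301 = 609, as stated.

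The rule can remove students only from the 301.

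**Step 3: how many.** Over 30% of ten sessions means more than three, so four or more missed. The article gives no expected attendance, so I assume a rate p per session, independent between sessions and students:

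P(miss at least 4) = sum over k = 4 to 10 of C(10, k) (1 − p)^k p^(10 − k)

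| Assumed p | P(miss at least 4) | Expected study exclusions (301 × P) | Chance of no exclusion, (1 − P)^301 | Control exclusions |
|---|---|---|---|---|
| 0.80 | 0.1209 | 36.4 | about 0 | 0 |
| 0.85 | 0.0500 | 15.0 | about 0 | 0 |
| 0.90 | 0.0128 | 3.9 | 0.02 | 0 |
| 0.95 | 0.0010 | 0.3 | 0.73 | 0 |

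**Step 4: two ways the arm could show.**
- *The analyst applies the rule.* The arm is visible directly, whatever the attendance rate.
- *Someone else applies it and passes on a file without attendance.* Only the one-sided loss remains as a clue. At p = 0.80 the planned sizes would become about 301 − 36 = 265 against 308, before any other loss. At p = 0.95 they would hardly change.

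The article does not say which of these is meant.

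**Step 5: what is still open at that point.** The normality judgement, the choice of pairwise test and the variables taken to the factorial ANOVA all depend on the data. The 30% threshold itself is stated in advance, but applying it is only a suggestion.

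**The case against.** The strongest reply is that nothing in the article makes the analyst apply the attendance rule. A second professional already holds the codes and could apply it before handing over a masked file. Who prepares a dataset is often left to an analysis or data-management plan. This stands in part. A reader might infer that blinding cannot hold, or that the analyst has to work with attendance, and the text supports neither. But the article does make a specific claim of blinding and gives participant coding as the means, and that means does not cover a variable its own analysis section uses.

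Three other stronger readings are also unsupported:

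- **Schools reveal the arm.** Table 1 puts each school in one arm, but the analysis section names type of school and course, not school identity. With arm and school coded, the analyst would see two sets of schools without knowing which is the study set.
- **Table 1 counts identify the arm for essentially all 609 students.** The ten pairs of grade counts do all differ. But they are planned counts, and consent, the class-attendance criterion, dropout and exclusions will change them. Several pairs differ by only a few students, and school totals already coincide across arms: 59 for schools 1 and 7; 56 for schools 4, 6 and 9. Were such matching reliable, coding the schools would not help either.
- **The ban on unmasking means results can never be tied to the programme.** The code holder knows the groups and could label finished results. The absolute wording needs a defined step, but it does not make the trial uninterpretable.

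Nor does the article show that choices would in fact be made with the groups visible, or that they would favour the programme. That is a risk. The outcomes are also not all equally open to reporting bias, since the knowledge test is multiple choice with correct answers.

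Last, keeping attendance from the analyst takes the 30% exclusion out of the main analysis. That is correct, and it has to be said openly.

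**Conclusion.** The concern holds in this form: the promised blind analysis is not secured as written. It relies on participant codes, while a planned exclusion uses a variable that exists in the study arm only, and no step keeps that variable from the analyst.

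That attendance exists in one arm, and that all exclusions fall there, follows from the text without assumption. The number of exclusions (about 36, 15, 4 or 0.3 of 301) rests on assumed attendance of 80%, 85%, 90% or 95% and on independence. Whether the arm would actually be seen depends on who applies the rule, which is not stated. The point should be corrected before post-baseline data reach the analyst; the documents do not show that any bias has arisen.

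**What to change.** Amend Allocation process, and Analytical methods to match:

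1. The professional who already holds the codes keeps the session-attendance file.
2. The analyst receives arm as A/B, with school and course as codes.
3. Test choices, including the normality rule, the pairwise test and the variables carried forward, are fixed and dated before post-baseline data are released to the analyst. This also protects against any remaining clue from group sizes.
4. The code holder reveals A/B once the main output is locked. This single step replaces the absolute ban on unmasking. Attendance-based analyses and integration with the qualitative results follow.
5. State openly that the main analysis includes all allocated students with data, and that the 30% attendance exclusion, which can remove only study-arm students, becomes a secondary analysis after the lock.

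If this is not done, delete the claim of a blind analysis.

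The procedural cost is protocol wording and a two-step data release using roles the article already has. The substantive cost is item 5: the analysed population changes. Under the attendance rates assumed above, about 0.3 to 36 study students who would have been dropped stay in the main comparison. That should be presented as a deliberate change, not as a detail of data handling.
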